## Abstract

**Background:**

Axillary lymph node dissection (ALND) in breast cancer causes substantial arm morbidity and long-term functional impairment. Less extensive axillary surgery, such as targeted axillary dissection (TAD), significantly reduces this risk. Although omission of ALND is standard in clinically node-negative disease with limited sentinel node involvement, this is not the case for patients with clinically node-positive disease undergoing upfront surgery. The aim of the SENOMAC-ULTRA trial is to evaluate whether TAD can safely replace ALND in patients with clinically node-positive breast cancer receiving upfront surgery.

**Methods:**

SENOMAC-ULTRA is a prospective, international, multicentre, randomized non-inferiority trial. Adults with stage II–III invasive breast cancer and axillary metastases detectable by ultrasound and confirmed by fine needle aspiration or core biopsy are eligible for inclusion. Participants are randomized 1 : 1 to TAD (removal of marked metastatic nodes plus sentinel lymph node biopsy) or standard ALND. The primary endpoint is recurrence-free survival, assessed for non-inferiority using a Cox proportional hazards model. Secondary endpoints include overall survival, locoregional recurrence, regional nodal recurrence, distant relapse-free survival, invasive breast cancer-free survival, patient-reported arm morbidity, and health-related quality of life, as well as performance measures of axillary ultrasound and marking techniques. A sample size of 1380 patients has been calculated to provide 81% power to exclude a hazard ratio > 1.47 for recurrence-free survival at 5 years, adopting a non-inferiority margin of 4.5%. Follow-up is planned for 10 years. The trial protocol has been approved by the Swedish Ethical Review Authority (Dnr 2025-07730-01); each participating country will obtain local ethics approval.

**Conclusion:**

It is anticipated that the SENOMAC-ULTRA trial will fill an important knowledge gap guiding the surgical management of patients with clinically node-negative breast cancer. Registration number: NCT06869629 (https://clinicaltrials.gov).

## Introduction

Axillary lymph node dissection (ALND) in breast cancer is the major contributor to significant arm morbidity and long-term negative impacts on patient-reported arm function^1–3^. Several prospective randomized trials have shown the non-inferiority of the omission of ALND in patients with clinically node-negative breast cancer who undergo primary surgery and are diagnosed with one to two metastases on sentinel lymph node biopsy (SLNB)^1,3–7^. However, the use of adjuvant radiotherapy (RT) and the eligibility of patients undergoing mastectomy varied among trials. In the SENOMAC trial, which randomly assigned patients with one to two macrometastases on SLNB to either completion ALND or its omission and reported non-inferiority of the de-escalated axillary surgical approach in 2024, 89% of patients in both groups received RT, including nodal target volumes^4,8^. Consequently, current international guidelines do not recommend completion ALND in this patient population^9^, whereas recommendations for adjuvant RT differ^10^.

Patients with axillary metastases detected before surgery have a higher nodal burden than those in whom metastases are identified on SLNB. In a study by Caudle *et al*.^11^, patients with T1–2 node-positive breast cancer, an abnormal axillary ultrasound (AUS), and positive fine needle aspiration cytology had a higher mean number of positive nodes (4.1 *versus* 2.2) and more often a pathological (p) N2–3 status (35% *versus* 11%) on ALND than clinically node-negative (cN0) patients undergoing SLNB before ALND. Still, 52% of patients had only one to two positive nodes overall^11^, a figure questioning the role of ALND. This was corroborated by another study^12^ in which 47% of cN0 patients with an abnormal AUS and a positive preoperative biopsy had only one to two positive nodes on ALND, a figure that increased to 59% for a single abnormal node on AUS.

Current National Comprehensive Cancer Network guidelines^9^ are for SLNB or targeted axillary dissection (TAD) in patients with limited nodal involvement on AUS and negative palpation planned for upfront surgery. Although TAD is a concept otherwise primarily used in the neoadjuvant setting, a similar strategy named tailored axillary surgery (TAS) is currently being tested in the TAXIS trial, which includes node-positive breast cancer both in upfront surgery and after neoadjuvant treatment. TAS is slightly different to TAD, being defined ‘by the sentinel lymph node procedure in combination with the selective removal of all palpable disease and documentation of the removal of the initially biopsy-proven and clipped lymph node metastasis by specimen radiography’^13^. Because intraoperative palpation and removal of obviously abnormal lymph nodes is part of SLNB, differences in nodal yield or precision are expected to be minimal. After TAS confirming node positivity, randomization is between regional nodal RT including the axilla and ALND plus regional nodal RT excluding the dissected axilla^13^. In an early analysis, the proportion of patients undergoing upfront surgery was 67.0% overall, but rates of primary systemic therapy increased significantly over time^14,15^. Another prospective trial addressing surgical de-escalation in clinically node-positive patients in the upfront setting is the announced randomized TADPOLE trial (NCT04671511), which will include patients with limited nodal involvement (one to two suspicious axillary lymph nodes).

The SENOMAC trial was intended^4^ to shed light on the question as to whether ALND could also be omitted in the subgroup of patients with an abnormal AUS and a confirmative preoperative biopsy; however, a negative clinical examination was mandatory. Overall, 347 patients with an abnormal AUS were registered, only 36 of whom had positive preoperative fine needle aspiration cytology. With these low numbers, it is impossible to assess this subgroup separately. Thus, the aims of the SENOMAC-ULTRA trial are to investigate the replacement of ALND with a TAD in clinically node-negative patients with a positive AUS and to broaden the inclusion criteria to clinically node-positive patients with cytological or histopathological confirmation of nodal involvement.

## Methods

SENOMAC-ULTRA is a prospective international multicentre randomized non-inferiority trial.

Adult patients scheduled for primary surgery for a primary invasive breast cancer clinical stage II–III with AUS-detectable axillary metastases confirmed by preoperative fine needle aspiration or core needle biopsy are eligible for inclusion (*Fig. 1*). Written informed consent is mandatory. Patients with inflammatory or locally advanced breast cancer or disseminated disease are not eligible for inclusion. In accordance with the Eight Edition of the AJCC Cancer Staging Manual^16^, the ‘clinical categorization of cancer is based on findings of history, physical examination, and any imaging studies that are done’. Eligibility criteria are presented in *Table 1*. Further clarification of the eligibility of specific clinical nodal stages is provided in *Table 2*.

**Fig. 1 zrag083-F1:**
[figure not shown]
Flow chart for eligibility and enrolment in the SENOMAC-ULTRA trial

**Table 1 zrag083-T1:** Eligibility criteria

Inclusion criteria	Exclusion criteria
Patients with primary invasive breast cancer clinical stage II–III Palpable or non-palpable axillary metastases visible by ultrasound (other imaging accepted if confirmatory ultrasound is performed) and confirmed by fine needle aspiration or core biopsy Written informed consent Age ≥ 18 years	Distant metastases Inflammatory or locally advanced breast cancer Ipsilateral metastases in internal mammary, infra- or supraclavicular lymph nodes without confirmed axillary nodal involvement Nodes fixed to each other or to neighbouring structures on palpation or imaging History of contralateral invasive breast cancer in the past 5 years Bilateral invasive breast cancer if: (i) any side meets any exclusion criteria; or (ii) both sides meet all inclusion criteria Pregnancy Preoperative systemic treatment (a short course of preoperative endocrine therapy < 3 months is allowed) Medical contraindications for or expressed preoperative wish to refrain from radiotherapy or the recommended adjuvant systemic treatment that complies with standard of care, taking age and co-morbidity into consideration Inability to absorb or understand the meaning of the study information (for example, through disability, inadequate language skills, or dementia)

**Table 2 zrag083-T2:** Eligibility of clinical nodal staging subcategories

Clinical nodal stage	Definition	Eligible
cN1	Metastasis in movable ipsilateral level I, II axillary lymph nodes	Yes
cN2a	Metastasis in ipsilateral level I, II axillary lymph nodes fixed to one another (matted)	No
cN2b	Metastasis only in clinically detected ipsilateral internal mammary nodes and in the absence of clinically evident level I, II axillary lymph node metastasis	No
cN3a	Metastasis in ipsilateral infraclavicular (level III axillary) lymph nodes with or without level I, II axillary lymph node involvement	Only if with axillary lymph node involvement
cN3b	Metastasis in clinically detected ipsilateral internal mammary lymph nodes and clinically evident axillary lymph nodes	Yes
cN3c	Metastasis in ipsilateral supraclavicular lymph nodes with or without axillary or internal mammary lymph node involvement	Only if with axillary lymph node involvement

Because the accuracy of AUS is highly user dependent, no specific maximum number of suspicious lymph nodes on AUS is applied. In the event of suspected extensive involvement of the axilla on AUS or other preoperative imaging modalities or on palpation during surgery, the performance of ALND is based on clinical judgement with or without intraoperative histopathological confirmation. An intraoperative or postoperative decision to perform ALND in a patient assigned to the intervention group does not lead to exclusion from the trial, but is documented in the trial database.

Criteria for suspicious nodes on AUS may vary between institutions and countries. As a guidance, a cortical thickness > 3 mm or the absence of a fatty hilum are recommended as the main criteria for the identification of metastatic lymph nodes by AUS. Representative still images of the most suspicious nodes should be stored and submitted to the central quality assurance database.

### Intervention

Patients assigned to the intervention group undergo TAD, which implies the removal of previously marked metastatic nodes plus SLNB, which includes the removal of stained and/or radioactive lymph nodes plus nodes that are clearly abnormal on intraoperative palpation. Marking of at least one biopsied nodal metastasis is mandatory and should ideally be performed after randomization. Any routinely used markers, such as clips, guidewires, carbon suspension, magnetic or radioactive seeds, radar reflectors, fluorescence detection, or radiofrequency identification tags, can be used. Marking of more than one node is optional. There is no maximum limit on the number of nodes that can be removed, but it is recommended that not more than four lymph nodes are removed.

In the event of localization failure, SLNB including the removal of clearly suspicious nodes on intraoperative palpation suffices. If multiple nodes have been marked, the identification of at least one is required. If neither the marked lymph node/s nor a sentinel lymph node can be identified during surgery, an ALND or representative sampling should be performed.

### Control

Patients assigned to the control group undergo upfront ALND of anatomical levels 1 and 2 with the aim of removing at least ten lymph nodes. Patients in whom the postoperative histopathology report identifies fewer than ten nodes are not excluded from the trial but are handled in sensitivity analyses.

### Endpoints, variables, and measures

The primary endpoint is recurrence-free survival (RFS) in accordance with STEEP 2.0 criteria^17^. RFS is measured from the date of randomization until the event date of any invasive local, regional, or distant breast cancer recurrence or death from any cause. Contralateral breast cancer is not defined as an event. Patients without any such event are censored at the date of last follow-up. This endpoint will be assessed for non-inferiority. The primary estimand is the hazard ratio of the time to local, regional, or distant breast cancer recurrence or death, comparing patients undergoing upfront TAD with patients undergoing upfront ALND among adults with primary stage II–III breast cancer and AUS-detectable axillary metastases.

Secondary endpoints are as listed below.

Overall survival is measured from the date of randomization until the date of death from any cause. Participants who are alive are censored at the date of last follow-up. This endpoint will be assessed for non-inferiority.Locoregional recurrence is measured from the date of randomization until the date of a local or regional recurrence, as defined above. This endpoint will be assessed for non-inferiority.Regional nodal recurrence is measured from the data of randomization until the date of a nodal recurrence in the ipsilateral axilla, supraclavicular, or internal mammary regions. This endpoint will be assessed for non-inferiority.Distant RFS is measured from the date of randomization until the date of any first distant recurrence, as defined above. This endpoint will be assessed for non-inferiority.Invasive breast cancer-free survival is measured from the date of randomization until the date of death from invasive breast cancer recurrence. Participants without a breast cancer recurrence will be censored at the date of death from other causes or the date of last follow-up, if still alive. This endpoint will be assessed for non-inferiority.Patient-reported arm morbidity will be assessed using the Lymphedema Functioning, Disability and Health questionnaire (Lymph-ICF), completed by study participants at baseline, annually for 5 years, and again after 10 years. This endpoint will be assessed for superiority at multiple time points (for example 1, 3, 5, and 10 years after surgery), including longitudinal analyses.Health-related quality of life will be assessed using the European Organisation for Research and Treatment of Cancer (EORTC) Core Quality of Life (QLQ-30) and Breast Cancer (BR-42) questionnaires completed by study participants at baseline, annually for 5 years, and again after 10 years. In addition, sense of coherence will be assessed using the SOC-13 questionnaire at baseline to allow adjustment of health-related quality of life outcomes for individual coping capabilities in challenging life situations. This endpoint will be assessed for superiority at multiple time points (for example 1, 3, 5, and 10 years after surgery), including longitudinal analyses.Performance measures of AUS will be evaluated documenting cortical thickness (millimetres), long- and short-axis diameter, the presence of a focal cortical bulge of > 3 mm, partial or complete effacement of the fatty hilum, and non-hilar cortical blood flow on colour Doppler imaging. The positive predictive value, sensitivity, and specificity of single and combined features for high nodal burden (four or more nodal metastases) will be evaluated. This endpoint will be assessed separately in the ALND group because ALND is necessary for determining high nodal burden.Performance measures of different markers in TAD will be evaluated by comparing the successful removal of the inserted marker between different marking strategies. This endpoint will be compared between different groups of marking strategies (for example, specific markers as well as visually guided identification *versus* probe-guided identification).

Further aims of SENOMAC-ULTRA are as follows:

evaluation of the SENOMAC nomogram^18^ predicting high nodal burden in patients with one to two sentinel lymph node macrometastases and its potential application to the SENOMAC-ULTRA population (a revised nomogram for high nodal burden will be created if necessary, incorporating AUS features readily available in routine care if proven to improve the nomogram’s predictive accuracy)assessment of the potential impact of axillary surgery on adjuvant systemic treatment (that is, both indications and the specific regimens)assessment of health economy by the EORTC QLQ-30 and EQ-5D-5L™ questionnaires annually for 5 years and again after 10 years.

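### The marker-performance endpoint counts removal of the marker, while TAD aims at the marked node, so comparisons that include guidewires, carbon or fluorescence can be biased

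*Protocol article*

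**What the plan says.** Two sections of the Protocol article bear on this.

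- **Endpoints, variables, and measures.** The last secondary endpoint evaluates markers by "comparing the successful removal of the inserted marker between different marking strategies". The example groupings are "specific markers as well as visually guided identification *versus* probe-guided identification". Retrieval of the node is not mentioned.
- **Intervention.** The procedure is described as "TAD, which implies the removal of previously marked metastatic nodes plus SLNB". The permitted techniques are wide: "Any routinely used markers, such as clips, guidewires, carbon suspension, magnetic or radioactive seeds, radar reflectors, fluorescence detection, or radiofrequency identification tags, can be used". The rule during surgery refers to the node: "If multiple nodes have been marked, the identification of at least one is required". Failure to localize is foreseen: "In the event of localization failure, SLNB including the removal of clearly suspicious nodes on intraoperative palpation suffices". Neither rule is tied to the marker endpoint.

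**The concern.** A marker is a means of finding the biopsied node, so a comparison of marking strategies should ask whether that node came out. The stated outcome asks whether the marker came out. How closely the second question stands in for the first depends on the physical nature of the marker:

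- **Guidewire:** it leaves the patient whether or not the node does, so its removal says little about localization.
- **Carbon suspension, fluorescence:** there is no discrete object, so removal is not a clear yes/no event.
- **Clip, seed, reflector, tag:** removal usually informs about the node, but a displaced marker can be retrieved without it (scored a success), or the node without the marker (scored a failure).

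At stake is the ranking of techniques, which could partly reflect what the marker is rather than how well it leads to the node. Node-level retrieval also has to be recorded at surgery and pathology. If only marker removal is captured, a later analysis plan cannot reliably reconstruct it.

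**Working it through.** **No figure to reproduce.** The article gives no retrieval rate, group size or power for this endpoint. The check is therefore the comparison of the two sections plus an illustration in which every rate is an assumption.

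**Inputs from the article**
- 1380 patients randomized 1:1, so 1380 / 2 = 690 in the TAD group (Estimated sample size and power; Randomization).
- Two-sided alpha of 0.05 for superiority endpoints (Statistical analysis), assumed here to apply to the marker comparison.

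**Assumptions**
- True retrieval of the marked node, *q*, is the same in both groups: 85%, 90% or 95%. A fair endpoint would show no difference.
- Guidewire removal, *w*, is 99%.
- Among patients whose node is missed, the other markers are still retrieved in a share *d*: 0, 25% or 50%.
- A node that is retrieved always brings its implanted marker with it.
- Wires are used in 100 or in 345 of the 690 patients.

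**Formulas**
- Endpoint for other markers: p = q + (1 − q)·d
- False gap: w − p
- Chance of a significant result: Φ[(gap − 1.96·SE₀)/SE₁], with SE₀ from the pooled proportion and SE₁ from the separate proportions.

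**One case in full** (q = 0.90, d = 0, 100 wires versus 590 others)
- p = 0.90; gap = 0.99 − 0.90 = 0.09
- Pooled proportion = (99 + 531)/690 = 0.913
- SE₀ = √[0.913 × 0.087 × (1/100 + 1/590)] = 0.0305
- SE₁ = √[0.99 × 0.01/100 + 0.90 × 0.10/590] = 0.0159
- (0.09 − 1.96 × 0.0305)/0.0159 ≈ 1.9, so the chance is 0.97

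**All cases**

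| q | d | p | False gap (points) | Chance significant, 100 v 590 | Chance significant, 345 v 345 |
|---|---|---|---|---|---|
| 85% | 0 | 85.0% | 14.0 | 1.000 | 1.000 |
| 85% | 25% | 88.75% | 10.25 | 0.992 | 1.000 |
| 85% | 50% | 92.5% | 6.5 | 0.803 | 0.989 |
| 90% | 0 | 90.0% | 9.0 | 0.972 | 0.999 |
| 90% | 25% | 92.5% | 6.5 | 0.803 | 0.989 |
| 90% | 50% | 95.0% | 4.0 | 0.395 | 0.870 |
| 95% | 0 | 95.0% | 4.0 | 0.395 | 0.870 |
| 95% | 25% | 96.25% | 2.75 | 0.200 | 0.660 |
| 95% | 50% | 97.5% | 1.5 | 0.080 | 0.323 |

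**How the result moves**
- Each point taken off *w* takes one point off the gap.
- If some retrieved nodes come out without their implanted marker, p falls and the gap widens.
- In the visual-versus-probe contrast, if wires make up a share *f* of one side and all other markers behave alike, the bias is f × gap. With f = 0.5 and a gap of 9 points it is 4.5 points; with f = 0 it is nil.
- The chances use a normal approximation, which is rough where few failures are expected (about one in 100 wires).

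**The case against.** The strongest reply is that this is one sentence on the last of nine secondary endpoints in a condensed article. It does not define what makes a removal successful, and the article defers further detail to the statistical analysis plan. The Intervention section speaks of nodes throughout and names localization failure as an event. A sympathetic reader would count a wire withdrawn without its node as such a failure, and would read removal of carbon as removal of the stained node. The unseen full protocol may say exactly that. This stands in part: if it does, only the article's wording needs aligning. But the article does state an outcome, the outcome names the marker, and nothing in the text links it to the node.

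Two stronger readings are tempting and are not supported:

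- **That guidewires score near 100% by construction.** This is inferred from how wires work. The documents give no rate for any marker, and the 99% above is an assumption.
- **That the visual-versus-probe comparison is invalid.** The article does not say which side wires or carbon join, or how many patients will have them. Marker removal remains a usable, if imperfect, outcome among implanted markers.

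Two further points against the concern also stand. The article does not label this endpoint as superiority or non-inferiority, so the significance test above is itself an assumption. And marker choice follows local routine rather than randomization, so the comparison is observational in any case. That limits what it can show, but does not justify an outcome that differs in meaning between groups.

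**Conclusion.** The concern holds as a defect in how one secondary endpoint is defined. Applied as written, marker removal does not measure the same thing across the permitted techniques, and comparisons that include wires, carbon or fluorescence can be biased. For wires the direction is favourable under the assumptions used. The size cannot be fixed from the documents: with equal node retrieval of 85–95% and wires at 99%, the false advantage runs from 1.5 to 14 points. The corresponding chance of a significant result runs from 8% to nearly 100% with 100 wires, and from 32% to nearly 100% with 345. Comparisons among implanted markers are less affected. Recurrence-free survival and the non-inferiority decision are not affected.

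**What to change.** Define success as excision of the marked biopsied node, with the marker, wire tip or stain documented in or on that node in the surgical or pathology report. The mere presence of a metastatic node in the specimen should not count as confirmation: every participant has a confirmed axillary metastasis, and TAD also removes sentinel and palpably abnormal nodes, so such a node need not be the marked one.

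Report marker retrieval and displacement of the marker from the node as separate descriptive items. If marker removal is kept as an outcome, report wires and carbon/fluorescence separately from implanted markers, and state which techniques count as visually guided and which as probe-guided.

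The cost is a change of endpoint wording and one or two eCRF items filled from surgical and pathology reports. Some cases will be indeterminate because the biopsied node cannot be identified; these should be counted and shown rather than assigned to success. The items need to be in place while patients are being operated on.
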